### **Convalescent plasma: regulatory issues.**

On March 20, the United States Food and Drug Administration (FDA) approved the use of convalescent plasma as single-patient emergency Investigational New Drug (eIND), a procedure adopted for drug with acceptable safety profile in case of urgent and life threatening conditions with no satisfactory available therapeutic alternatives. The American Association of Blood Banks (AABB) launched a new website as an educational resource to inform the public, blood collectors and clinicians about COVID-19 convalescent plasma (CCP). The aim was to inform and motivate people who had recovered from COVID-19 about donation of convalescent plasma to help improving the status of critically ill patients with COVID-19. FDA indicated that convalescent plasma had to contain an adequate level of SARS-CoV-2 neutralizing antibody titer (e.g., greater than 1:80). Nevertheless, if neutralizing antibody titer could not be determined before donation, FDA invited blood bank to store a retention sample from the convalescent plasma donation for determining antibody titers at a later date. In the meanwhile, AABB released a

protocol to assist facilities in the collection of CCP. American Association of Hematology (ASH) released an information on the same topic, reporting that individual physicians had begun to treat patients with serious COVID-19 disease with convalescent plasma collected by blood centers (according an eIND procedure). In the meanwhile, multicenter clinical trials, focusing on either prophylaxis of high-risk individuals, treatment of those with serious but not critical COVID-19 disease, or treatment of critically-ill ICU patients, were designed. The ASH information clearly reports that use of plasmapheresis to collect large volumes of plasma would be desirable, allowing to treat at least 2-3 recipients by one collection. In addition, quantitative serologic assays are not yet widely available to identify convalescent patients with high titer neutralizing antibodies. Until the time of writing, no official documents have been published on the CCP by the Italian National Blood Centre (Centro Nazionale Sangue (CNS). Nevertheless, current CNS recommendation for blood donor selection during the COVID-19 pandemic, allows individuals with recent COVID-19 infection to donate after 14 days from symptoms cessation and therapy discontinuation. The Italian Society for Apheresis (SIDEM) and the Italian Society of Transfusion Medicine (SIMTI) released a joint position statement endorsing the collection of “hyperimmune convalescent plasma” by Italian blood banks. Hyperimmune convalescent plasma or equivalent definitions are not mentioned in the last version of the “Guide to the preparation, use and quality assurance of blood components”. In the SIDEM/SIMTI document, hyperimmune plasma is defined as the plasma product containing an antibody titer against SARS-CoV-2 higher than 160 at enzyme immunosorbent assay or equivalent tests. This definition was drawn by a Saudi Arabian interventional single group study (ClinicalTrials.gov Identifier: NCT02190799) on convalescent plasma therapy in critical MERS-CoV patients. The study started in 2014 and was withdrawn in 2018. While to our knowledge no results have been published, investigators published the study protocol in which measurement of anti-MERS-CoV antibodies level in donor and participant serum through commercially available kits is recommended. At the time of writing, no commercially available methods to measure anti SARS-CoV2 antibodies are available, either based on ELISA or neutralization

assays. Moreover, the equivalence between presence of an adequate titer of neutralizing antibody (NAT) and ELISA detectable antibodies is not straightforward. For example, studies on Ebola virus infection showed that 90% or more among convalescent plasma donors exhibited high IgG and IgM levels at ELISA, whereas only 5% of them had high NAT. Conversely, among 881 convalescents from H1N1 pandemic influenza, a high NAT (> 1:40) was found in more than 90% of individuals and was associated with more severe disease, with higher levels in patients experiencing pneumonia in comparison with those with afebrile presentation (OR 3.39; 95% CI 1.49-7.61). Similar findings were reported in a small number of patients with MERS-CoV infection, with patients with pneumonia showing long lasting antibody titers >40. Therefore, donor selection should rely on the anamnestic basis, in order to identify donors potentially exhibiting high NAT. Finally, it should be emphasized that the majority of studies reporting a positive effect of convalescent plasma against SARS-CoV, H1N1 and H5N1 do not report the NAT of transfused plasma. Indeed, whereas it is conceivable that convalescent plasma donors might exhibit variable levels of NAT or ELISA-dosed antibodies, an evidence-based higher efficacy of “hyperimmune” plasma (as defined by the SIDEM/SIMTI document) is still lacking.

## **RATIONALE**

Our hypothesis is that transfusing COVID-19 convalescent plasma (CCP) to elderly patients with COVID-19 pneumonia and comorbidities might prevent the evolution to severe disease. At present, no single specific vaccine, nor specific antiviral therapy against COVID-19 can be used to modify the clinical course of this disease. COVID-19 can present with different severity of symptoms and can be categorized as mild, severe, or critical COVID-19. Mild COVID-19 includes non-pneumonia and mild pneumonia cases (with no need for oxygen supplementation). Severe COVID-19 is characterized by dyspnea, respiratory frequency  $\geq 30$ /minute, blood oxygen saturation  $\leq 93\%$ , PaO2/FiO2 ratio  $< 300$ , and/or lung infiltrates increasing  $> 50\%$  within 24–48 hours). Critical COVID-19 includes respiratory failure, septic shock, and/or multiple organ dysfunction/failure, including acute kidney injury and cardiac injury. An important lesson learned from initial reports on hospitalized patients is

that COVID-19 rapidly deteriorate in specific categories of patients. Poor prognosis patients are aged over 60, are mainly man and near half of them have some comorbidities. In-hospital death is associated with older age, higher Sequential Organ Failure Assessment (SOFA) score and blood d-dimer greater than 1 µg/mL. These findings are known to be associated with severe pneumonia. Although current best estimate is that about 81% of people with COVID-19 have mild disease and never require hospitalization, 14% of patients have severe illness and need oxygen therapy, and approximately 5% require intensive care treatment and mechanical ventilation. Since the reported case fatality rate ranges from 49% to 97% in critical patients, it is pivotal to find alternative strategies to prevent older patients and patients with chronic morbidities from worsening. The association between severe COVID-19 and specified patient characteristics has emerged from the analysis of large patient population and from meta-analysis of recently published studies. Older age is an independent poor outcome predictor in hospitalized patients (odds ratio 1.10, 95% CI 1.03–1.17 per year increase). Among 72,314 COVID-19 cases, case fatality rate was 2.3% in total population, 8% in people aged 70 to 79, and 14.8% in those aged 80 and older. In the whole population, case-fatality rate was higher in people with comorbidities, ranging from 5-6% in persons with hypertension, chronic respiratory disease, diabetes or cancer, up to 10% in those with cardiovascular diseases. On the other side, one or more comorbidities was reported in 36/54 (67%) poor outcome COVID-19 patients as compared to 55/137 (40%) survivors ( $p=0.0010$ ). These overall data show that elderly people with comorbidities are most susceptible to severe COVID-19 and therefore, should be protected by approaches which may supplement current therapies. Data relative to the long lasting persistence of the virus in patients with poor outcome, together with the presence of lymphopenia (CD4+T and CD8+ T cells) and exaggerated pro-inflammatory and anti-inflammatory cytokines (IL-2R, IL-6, TNF- $\alpha$  and IL-10) suggest that disease severity and outcome of COVID-19 is due to the SARS-CoV-2-induced cytokine storm. Sars-CoV-2 seems able to induce a functional exhaustion of specified T and NK lymphocyte subpopulations, breaking down antiviral immunity. One possible explanation is that the immune system of elderly people,

exposed to chronic stimulation associated with comorbidities, might be more susceptible to this Sars-CoV-2 effect. As a result, in these patients, the activation of the innate immune system might fail to produce an adequate adaptive response (i.e., virus-specific CD8+ T-cells). This could result in a persistent self-induced inflammation that then causes mortality. We therefore hypothesize that transfusing the convalescent plasma containing neutralizing antibodies at an early phase of disease could prevent or switch-off the persistent inflammatory response elicited by the virus, before that cytokine storm exerts devastating effects. As a proof of concept that CCP has an activity on the infection, in enrolled patients we will assess the viral load in blood and nasopharyngeal swab before and plasma infusion.

## BENEFIT / RISK ASSESSMENT OF THE TREATMENT

Benefit of CCP. Potential benefit of CCP is to prevent progression of COVID-19 to a more severe form. Benefit of plasma infusion are conceivably connected with the presence of specific antibodies against the virus. At the time of writing, there are no validated commercially available tests to determine the NAT against SARS-CoV2 in collected units. Nevertheless, as soon as methods for NAT or ELISA determination will be available, CCP will be selected on the basis of the antibody titre in order to select units with higher activity.

Risks of CCP. Potential risks connected with the use of CCP are those relative to general blood transfusion and include allergic/febrile reaction (estimated frequency 1 in 100), transmission of infectious disease (HIV, HBV, HCV, syphilis, etc.; estimated frequency 1 in 1.000.000), transfusion associated circulatory overload (TACO, estimated frequency 1 in 100) and transfusion associated acute lung injury (TRALI, estimated frequency 1 in 100.000). Hemolytic non severe reactions could also occur if ABO incompatible plasma is transfused. Any precaution will be undertaken to minimize these risks. Transfused CCP will fulfil all current quality and safety requirements for blood products will be collected according to CNS recommendations for blood donor selection during the COVID-19 pandemic. All units will be subjected to pathogen inactivation by Intercept technology. To prevent TRALI, female donors who had pregnancies or donors who received transfusions will be not allowed to donate. An additional theoretical risk is that antibody anti-SARS-CoV-2 might prevent patients from their active immunization. For this reason, the trial will test patients for serology for SARS-CoV-2, and if negative, they should be vaccinated when anti-SARS-CoV-2 will be available. Finally, a phenomenon named “Antibody Dependent Enhancement” (ADE) of infection has been observed in in vitro studies, infecting cells with different types of viruses in presence of specific antibodies. Theoretically, ADE might worsen infection in COVID-19 patients. It is unknown, however, if ADE might occur in vivo in COVID-19 patients and several clinical studies have reported that SARS-CoV-specific antibodies found in SARS patients are not harmful in this regard.

## OBJECTIVES AND OVERALL STUDY DESIGN

|                      |                                                                                                                                                                                                                                                                                                                                                                                                                                                                                                                                                                                                                                                                                                                                                               |
|----------------------|---------------------------------------------------------------------------------------------------------------------------------------------------------------------------------------------------------------------------------------------------------------------------------------------------------------------------------------------------------------------------------------------------------------------------------------------------------------------------------------------------------------------------------------------------------------------------------------------------------------------------------------------------------------------------------------------------------------------------------------------------------------|
| Objectives    | The primary objective of this study is to demonstrate that COVID-19 convalescent plasma (CCP) may prevent progression to severe pneumonia in elderly COVID-19 pneumonia patients with chronic comorbidities.                                                                                                                                                                                                                                                                                                                                                                                                                                                                                                                                                  |
| Trial design  | This is a randomized phase II/III study designed to evaluate the efficacy of convalescent plasma, when used in combination with standard therapy to prevent the progression of pneumonia in elderly COVID-19 patients with comorbidities. The trial will start with a screening Phase II trial designed with two-tailed $\alpha=0.2$ . In case of positive result the trial will proceed in a formally comparative phase III trial ( $\alpha=0.05$ ). Three studies have so far reported the use of CCP in ventilated patients without recording adverse events, but data on patients in earlier phase of disease are lacking. For this reason, the first 57 patients will be observed in order to assess preliminarily the safety of CCP in this population. |
| Study setting | Participating centers are: 

– Fondazione Policlinico Gemelli IRCCS (coordinating center)

– Istituto Nazionale Malattie Infettive Lazzaro Spallanzani IRCCS

– Ospedale SS Annunziata, Chieti

                                                                                                                                                                                                                                                                                                                                                                                                                                                                                                    |

## ELIGIBILITY CRITERIA

|                           |                                                                                                                                                                                                                                                                                                                                |
|---------------------------|--------------------------------------------------------------------------------------------------------------------------------------------------------------------------------------------------------------------------------------------------------------------------------------------------------------------------------|
| Study population   | Adult patients with confirmed or suspected COVID-19 who are at risk according to CDC definition are eligible for the study.                                                                                                                                                                                                    |
| Inclusion criteria | All the following 

– Age <math>\geq 65</math>

– pneumonia at CT scan

– <math>\text{PaO}_2/\text{FiO}_2 \geq 300</math> mmHg

– Presence of one or more comorbidities (consider the list provided in Appendix A)

– Signed informed consent

 |
| Exclusion criteria | One of the following 

– Age <math>< 65</math>

                                                                                                                                                                                                                         |

- PaO2/FiO2 < 300 mmHg
- pending cardiopulmonary arrest
- refusal to blood product transfusions
- severe IgA deficiency
- any life-threatening comorbidity or any other medical condition which, in the opinion of the investigator, makes the patient unsuitable for inclusion.

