| Phase III endpoints | 
Primary
 
 
– Proportion of patients without progression at day 14
 
 
Secondary
 
 
– Viral load on nasopharyngeal swab at days 6,9 and 14
 
– Viremia at days 6 and 9
 
– Antibody titer against SARS-CoV2 at days 30 and 60
 
– Proportion of patients with negative of SARS-CoV2 nasopharyngeal swab at day 30
 
                                                |
| Study population    | Adult patients with confirmed COVID-19                                                                                                                                                                                                                                                                                                                                                                                                                                                                     |
| Inclusion criteria  | 
Inclusion criteria are all the following:
 
 
– Age <math>\geq 65</math>
 
– evidence of pneumonia by CT scan
 
– <math>\text{PaO}_2/\text{FiO}_2 \geq 300</math> mmHg
 
– Presence of one or more comorbidities (list provided in annex 1)
 
– Signed informed consent
 
                                                                                                                                            |
| Exclusion criteria  | 
Exclusion criteria include one of the followings:
 
 
– severe COVID-19 disease
 
– <math>\text{PaO}_2/\text{FiO}_2 < 300</math> mmHg
 
– impending cardiopulmonary arrest
 
– refusal to blood product transfusions
 
– severe IgA deficiency
 
– any life-threatening comorbidity or any other medical condition which, in the opinion of the investigator, makes the patient unsuitable for inclusion
 
 |

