#### Screening phase: day -1

#### Baseline visit: day 0:

Physical examination and vital signs (blood pressure, heart rate, respiratory rate, temperature), Respiratory status (pO2/FiO2 and SpO2 at rest if applicable), ECG; blood sampling for ABO groups (on two separate samples), RT-PCR for SARS-CoV-2 on nasopharyngeal swab. routine blood tests (blood count, creatinine, BUN, sodium, potassium, ALT, AST, LDH, fibrinogen, D-dimer, ferritin, CRP), viremia, anti SARS-Cov-2 antibody screening, IL6.

**Plasma administration: days 1,2, 3.** All patients will sign the informed consent to receive blood products in use at each center.

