**Statistical methods Primary endpoint:**

Based on the above-mentioned design, the comparison of proportion of progression free patients will be made between A vs B through the Fisher exact test at the completion of phase II and phase III.

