**Secondary endpoints**

Descriptive results will be presented as means  $\pm$  standard deviation (SD), medians with interquartile range (IQR), and percentages with 95% confidence intervals (CI). Chi-square or Fisher's exact test will be used to compare categorical variables. ANOVA and Student's t-test will be used for continuous variables unless they will be not normally distributed, in which case the Kruskal-Wallis or Mann-Whitney test will be used to compare continuous parameters. Kaplan-Meier product-limit estimates will be used to calculate time to different secondary endpoints. The log-rank test will be used to assess the difference between the survival curves among arms. Changes in some biomarkers respect to baseline values will be compared using paired Wilcoxon test. The association between primary outcome and transfusion dose of CCP expressed as ml/kg of the recipient body weight, adjusted for anti-Sars-CoV-2 neutralizing and ELISA antibody concentrations, will be investigated through regression analysis. All tests will be two-sided and a P value inferior to 0.05 will be regarded as significant.

**Analysis settings** Analysis will be carried out in the "intention to treat" set.

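### The eligibility section admits suspected COVID-19 where the synopsis requires confirmed disease, and no positive test is an entry condition, so uninfected patients may enter the intention-to-treat comparison

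*Protocol*

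**What the plan says.** The Study population row of the synopsis reads "Adult patients with confirmed COVID-19". The same row in the Eligibility Criteria section reads "Adult patients with confirmed or suspected COVID-19 who are at risk according to CDC definition are eligible for the study". Both are current text.

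Each inclusion list asks for age 65 or over, pneumonia on CT, PaO2/FiO2 of at least 300 mmHg, a listed comorbidity and consent. The disease-defining item is "evidence of pneumonia by CT scan" in the synopsis and "pneumonia at CT scan" in the eligibility section. Neither list names a virological test, and no exclusion removes a patient who tests negative.

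The day 0 baseline visit includes "RT-PCR for SARS-CoV-2 on nasopharyngeal swab". No text makes a positive result a condition of entry or says what happens to a patient whose result is negative.

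The primary comparison is made "through the Fisher exact test at the completion of phase II and phase III", and the only analysis set named is intention to treat.

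The exclusion lists also differ: the synopsis excludes "severe COVID-19 disease" and the eligibility section has no such item.

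**The concern.** Sites working from the two pages could enrol different populations. The rest of the protocol presumes infection. The rationale rests on neutralising antibody, change in viral load is offered as the proof of concept, and viral load on swab is a secondary endpoint in both phases.

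A randomised patient who is not infected cannot gain from antibody to this virus, yet intention to treat keeps that patient in the primary comparison, which pulls the estimated difference towards zero. On the Phase III secondary outcome of a negative swab, such a patient counts as a success in either arm, whatever the treatment. In Arm A the patient would also be exposed to three plasma infusions, for which the Benefit/Risk section estimates allergic or febrile reaction and circulatory overload at about 1 in 100 each.

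Eligibility is fixed in the protocol, so a statistical analysis plan cannot resolve the contradiction.

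**Working it through.** **Inputs.** From the Sample size section: Phase III, progression 40% in control against 20% with plasma, two-sided alpha 0.05, 80% power, 91 per arm; Phase II, patients without progression 20% against 40%, two-sided alpha 0.2, 80% power, 57 per arm. Allocation is 1:1. The Statistical methods section gives Fisher's exact test.

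**Reproducing the stated sizes.** The uncorrected two-proportion formula is

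n = [z(α/2)·√(2·p̄·(1−p̄)) + z(β)·√(p1(1−p1) + p2(1−p2))]² / δ²,

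followed by the continuity correction n′ = (n/4)·[1 + √(1 + 4/(nδ))]². Here p̄ = 0.3 and δ = 0.2.

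- Phase III: (1.960 × 0.648 + 0.842 × 0.632)² / 0.04 = 81.2. The correction gives 90.9, so 91 per arm, as stated.
- Phase II: (1.282 × 0.648 + 0.842 × 0.632)² / 0.04 = 46.4. The correction gives 56.0, so 56 per arm against the stated 57.

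The stated sizes are therefore the plain two-proportion sizes, with nothing added for uninfected patients. Exact Fisher power, summed over all pairs of binomial outcomes, is 80.7% at 57 per arm and 80.8% at 91 per arm.

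**Dilution model (assumption).** Let a share f of each arm be uninfected, gain nothing from plasma and progress with probability u. Then

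- control progression = 0.40(1−f) + u·f
- plasma progression = 0.20(1−f) + u·f
- difference = 0.20(1−f)

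For example, f = 10% and u = 40% gives 0.36 + 0.04 = 40% against 0.18 + 0.04 = 22%. The protocol gives neither f nor u, so both are varied.

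| f | u | Progression, control vs plasma | Phase III Fisher power, 91 per arm | Phase II Fisher power, 57 per arm |
|---|---|---|---|---|
| 0 | – | 40% vs 20% | 80.8% | 80.7% |
| 5% | 40% | 40% vs 21% | 75.8% | 76.9% |
| 5% | 0% | 38% vs 19% | 77.7% | 78.4% |
| 10% | 40% | 40% vs 22% | 70.4% | 72.8% |
| 10% | 0% | 36% vs 18% | 74.3% | 76.0% |
| 20% | 40% | 40% vs 24% | 58.6% | 63.9% |
| 20% | 0% | 32% vs 16% | 66.6% | 70.7% |

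**The other reading of the rates.** The Phase II text, read literally, means progression of 80% against 60%. At f = 10%, Phase II power is then 74.1% if the uninfected progress at 80% and 70.9% if they never progress. The two readings together give about 71–76%. The synopsis words Phase III in this way too. On that reading Phase III power at f = 10% would be 72.3% or 67.0%, so the 40% against 20% figures are not the harsher choice.

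**Size needed to restore 80% power** (same formula, Phase III, 40% vs 20%): 106 to 114 per arm at f = 10% and 123 to 145 at f = 20%, against 91 planned.

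**The case against.** The strongest case on the other side is that few uninfected patients would enter. Recruitment is at COVID centres, the objective speaks of COVID-19 pneumonia patients, the synopsis already requires confirmation, a swab is taken at day 0, and the investigator may exclude anyone judged unsuitable. The sample size is also stated in evaluable patients. This limits the likely share, but it does not remove the contradiction: no sentence ties the swab to entry, and evaluable is not defined as infected. It does mean that the power figures are scenarios and not forecasts.

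Four stronger readings are tempting, and the protocol does not support them:

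- A reader might infer that any older patient with another pneumonia qualifies. The eligibility section still requires COVID-19 to be confirmed or suspected, and the patient to be at risk by the CDC definition. The exposure is to suspected cases that prove negative.
- A reader might infer that uninfected patients have no swab outcome. They have one, and it is an automatic success.
- A reader might infer that PaO2/FiO2 is the eligibility section's only bar to sicker patients. It also excludes pending cardiopulmonary arrest and life-threatening comorbidity, and it allows investigator judgement.
- A reader might infer that patients with already severe disease can enter freely. The Rationale's description of severe disease includes PaO2/FiO2 below 300, which both lists exclude. Its items are joined by commas and a final and/or, so whether one other sign alone makes a case severe is not settled.

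**Conclusion.** The concern holds as an internal contradiction on confirmation of infection, and the text is wrong as written whatever the share of uninfected patients turns out to be. The direction of the effect is clear: power fell in every scenario computed, from a starting point of only about 81%.

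The size is conditional. If 10% are uninfected and gain nothing, Phase III power is 70–74% and Phase II power about 71–76%. At 20%, Phase III power is 59–67%. The Phase III ranges assume 40% against 20% progression in infected patients, with uninfected patients progressing at anything from 40% down to 0%. The Phase II range covers both readings of its rates. Confidence is high for the textual conflict and limited for the magnitude.

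The difference between the exclusion lists on severe disease is a separate and narrower mismatch, and no size is claimed for it.

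**What to change.** Delete the reference to suspected cases in the Study population row of the Eligibility Criteria section, so that it matches the synopsis. Add laboratory-confirmed SARS-CoV-2 infection to both inclusion lists, shown by the swab already scheduled for day 0 or by an earlier positive result, and state that randomisation follows the result. With that change the stated sample sizes stand.

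The cost is an amendment of a few words, a short wait before randomisation and the loss of some patients with false-negative tests. The protocol states neither the turnaround of the test nor the moment of randomisation, so the sponsor should confirm that the result can be available before the first infusion on day 1.

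If the sponsor does want suspected cases, both places should say so. The protocol should then pre-specify an analysis in patients with infection confirmed at baseline, and restate the power or sample size for an assumed uninfected share.

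Separately, reconcile the two exclusion lists on severe disease. Which version applies is for the sponsor and the investigators to decide.
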